### Ethical approval

Approval to undertake this project was obtained from a number of Agencies, namely:

1. Royal Prince Albert Hospital Ethics Committee, Sydney, NSW, Australia. Reference Number – X09 – 0052 & HREC 09 / RPAH/ 85.

2. University of Newcastle Research Ethics Committee, NSW, Australia. Reference Number – H- 2012 – 0070.

3. AH & MRC Ethics Committee, NSW, Australia. Reference Number – 696 / 09.

### Dental health education program

The visit program is outlined in Figure
1 and centres on avoiding using a ‘bottle’ as a night –time comforter, using fluoride toothpaste from 9 months of age, encouraging the whole family to brush and having a simple oral health screening by the AHWs to assess whether early signs of dental caries are evident. Culturally appropriate leaflets and fridge magnets will be offered and an advice line is available should any of the families have specific problems. An example of one of the leaflets is shown in Figure
2.

**Figure 1 F1:**
[figure not shown]
Dental health education program for Aboriginal families, beginning at six months and following on with advice from AHWs over time.

**Figure 2 F2:**
[figure not shown]
An Example of a leaflet to be given to Families participating in the program – focus on not using a night-time bottle.

### Data collection

Information on baseline and subsequent visits (Figure
1) will be collected by the AHWs utilizing a structured questionnaire which has been piloted in an Aboriginal community.

The key topics for intervention are:

Bottle use, when and what to put in it.

Tooth brushing – using the tooth brush

Toothpaste - using the toothpaste, how much to put on the brush and safe storage

Dietary habits – reported changes in the consumption of sugary snacks and drinks

AHWs screen for caries
[35] – positive/negative

Reported dental problems

At the final 30-month assessment the carers will be asked about their perceptions of the feasibility, and acceptability of the program. In addition selected questions from the Dental Discomfort Scale
[36] and the Being a Mother Scale
[37] will be included in the assessment. The Aboriginal Health Workers and the senior management team at each AMS will be interviewed to record their views on the facilitators and barriers to the wider implementation of the program. All interviews will be recorded, transcribed and analyzed for recurrent themes.

The end of trial dental assessment will be undertaken by a calibrated examiner using the same diagnostic criteria when collecting the dental caries data on the historical reference group.

### Statistical analysis

The primary analysis will be an evaluation of the estimated prevalence of caries at 30 months in relation to the null hypothesis that the rate is 2. Descriptive analyses of other endpoints will be applied using methods appropriate for continuous and categorical data. Estimates will be presented with two-sided 95 percent confidence intervals.

The qualitative data from the interviews will be analyzed , using the ‘framework’ method
[38]. The qualitative data will be fractured and examined for key topic areas. The data will then be systematically coded according to the topic areas and thematic charts (in spreadsheet form) will be constructed. Summaries of the relevant parts of transcripts will be written into the charts so that each case may be examined across a range of different and emerging themes
[38].

The proposed study is rare in health promotion research in that it is not a ‘before and after’ design but is longitudinal, building information and capacity over time
[39]. The longitudinal design helps the investigative team to test for mediation effects in a more rigorous manner than cross sectional designs
[40]. For example the multi-wave nature of the assessments delivers the following methodological advances:

i. prevention on the reliance of retrospective reports of health behavior from mothers (removal of memory biases);

ii. reliable baseline latent variables of fluoride use and oral health (reducing bias of measurement error);

iii. enable the testing of growth models and unbiased parameter estimation of the fluoride intervention using resampling methods (bootstrapping). This third improvement would be made possible by controlling for concurrent baseline disease levels. Cole and Maxwell
[39] suggest that Structural Equation Modelling (SEM) will greatly assist in testing the direct and indirect effects of a longitudinal intervention. Crucial is the development of a model which can reduce bias frequently inherent in two wave designs. These are sometimes referred to as ‘half-longitudinal’
[41]. The proposed design therefore has innovative features not utilized in previous caries prevention programs which will enable true longitudinal investigation benefiting from the latest developments in statistical modeling.

One potential model which could be assessed utilizing Structural Equation Modeling is shown in Figure
3. The circles denote latent variable specification and the rectangles represent raw variables. Single indicator raw variables are permitted in SEM if the reliability estimate for the item is known. These estimates will be available from pilot work and previous published evidence. The arrows show theoretically derived effects specified for detailed examination in the statistical modeling. In addition, the model as depicted in Figure
3 can test for supplementary effects which are not possible in simple baseline and single post-intervention assessment designs.

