## Methods/Design

The aim of the program of research is to address the need to improve the oral health of Aboriginal children
[10-12]. The objective of the study is to build upon the success of the pilot work, using a phase II single arm trial design to gather preliminary evidence on the effectiveness of the program offered to Aboriginal children from six months of age who are at risk of dental caries. The program will be assessed over a period of 2 years to investigate not only the effectiveness, but also its feasibility and to inform the design of a subsequent confirmatory randomised phase III trial. The research follows the MRC framework for the design and evaluation of complex interventions to improve health
[13]. The primary endpoint is the prevalence of early childhood caries at 30 months of age. Secondary endpoints include: changes in primary caregivers dental knowledge over time; number of episodes of dental care; impact of oral health problems on the family and qualitative measures of the program to assess its acceptability to the families. In addition the managers and Aboriginal Health Workers will be interviewed to record their views on the overall feasibility and sustainability of the program
[14].

The pilot work and consultation with ACCHSs led to the development of the dental health education program which is characterized by the following strategies:

Delivery by trained Aboriginal Health workers;

Support for health oral behaviours offered to families with young children;

Focus on control of the night time bottle, toothbrushing and use of fluoride toothpaste;

Free toothpaste, and toothbrushes for all the family together with a ‘sippy’ (trainer) cup for the child;

Restricting the frequency of the consumption of sugary snacks and drinks.

Careful attention to the cultural appropriateness of teaching materials.

The development of the ACCHSs capacity to provide oral health support to vulnerable families through the development of the role of AHWs is based on Goodman’s model of organizational change
[15].

The development of the oral health role of Aboriginal Health Workers is strongly supported by the National Aboriginal Community Controlled Health Organisation
[16], the Australian Dental Association
[17], Australia‘s National Oral Health Plan
[18], and the National Aboriginal and Torres Strait Islander Oral Health Workshop

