[27]. A study of Northern Territory Aboriginal communities reported that only 20 percent of children used toothpaste daily and most did not begin using toothpaste until the age of four
[28]. The AIHW reports that ‘Less than 5 percent of remote Aboriginal and Torres Strait Islander pre-school children brush their teeth on a regular basis
[6]. Causes identified for low use of toothbrushes and fluoride toothpastes include poor levels of carer education, high purchase costs and difficulties in establishing tooth brushing routines. The proposed program addresses these crucial barriers to the prevention of early childhood caries in Aboriginal families. AHWs will provide vulnerable families with advice on effective tooth brushing, use of fluoride toothpastes and support the development of these behaviours by the distribution of oral hygiene products and materials including toothbrushes, fluoride toothpaste and trainer cups
[29]. These preventive strategies are based on high quality evidence derived from large population based randomized controlled trials and systematic reviews
[30] and show a benefit when used over time. Therefore the theoretical construct underpinning the program is the tailoring of the oral health message to the specific oral health and psychosocial needs of Aboriginal families and their children
[31].

The dental health education program and the research instruments have been piloted with Aboriginal families, Aboriginal Health Workers and aligns with the Aboriginal Health and Medical Research Council policies on partnerships with Aboriginal Communities.

The primary endpoint for the study will be:

The prevalence of ECC at the age of 30 months. These data will be compared with similar children aged 30 months participating in the Aboriginal communities in the first year of the program implementation.

The secondary endpoints include:

Changes in the oral health knowledge of the primary care giver over time.

Early referral for dental care, if the oral health screening by the Aboriginal health workers notes a problem.

Impact of the child’s oral health on the family.

Acceptability of the program recorded by interviewing parents and AHWs at the end of the program.

Sustainability assessed by interviewing managers of the participating Aboriginal Community Care Health Services.

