### Study design

The study is designed to monitor a longitudinal oral health education program for Aboriginal children aged 6 months followed for 2 years. In order to assess the effect on dental caries, a sample size of 150 participants will provide at least 80 percent power at the two sided 95 percent level of significance to distinguish between a prevalence of 2 versus 1.6 ECC ( ECC includes decayed ,missing and filled primary teeth ) at 30 months allowing for as much as a 33% attrition rate (chosen following discussions with AHWs on population movement). The reference rate for ECC is informed by data provided by the Centre for Oral Health Strategy, New South Wales (personal communication and work by Jamieson et al
[6]). The forward projection is that the participating children will have a reduction in the mean ECC score of 20 percent, to 1.6. This is highly plausible and is based on previous trials. For example a recent study where fluoride toothpaste was posted to families living in low socio-economic areas of Northern England reported a 16 percent reduction in dental caries in young children
[32]. No personal advice was offered. An Australian study reported a 33 percent reduction in dental caries
[33,34], following a health education program which included the application of topical fluoride.

The rejection of the null hypothesis will be considered indicative of a clinically significant benefit, and would provide a strong case for proceeding to a Phase III evaluation.

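### The primary endpoint is called a prevalence, but its null (2), target (1.6) and 80% power fit only a mean tooth count per child

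*Protocol article*

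**What the plan says.** The opening text of Methods/Design in the protocol article states: "The primary endpoint is the prevalence of early childhood caries at 30 months of age". The endpoint list later in that section repeats it: "The prevalence of ECC at the age of 30 months".

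Study design gives the size: "a sample size of 150 participants will provide at least 80 percent power at the two sided 95 percent level of significance", in order to "distinguish between a prevalence of 2 versus 1.6 ECC", with a bracketed note that ECC covers decayed, missing and filled primary teeth, and with an allowance for 33% attrition. The same paragraph then describes the expected effect as a "reduction in the mean ECC score of 20 percent, to 1.6".

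Statistical analysis sets the primary analysis as an "evaluation of the estimated prevalence of caries at 30 months in relation to the null hypothesis that the rate is 2".

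No section gives a null or target proportion, an SD or distribution for the tooth count, or a definition under which prevalence means a count. The Background, where it says how common caries is, uses a percentage of children affected (43%).

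**The concern.** A prevalence is a proportion of children and lies between 0 and 1, so it cannot be tested against 2. A mean number of affected teeth per child can. The article uses one word for both measures in the endpoint definition, the power statement and the primary analysis.

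The two measures can give different answers. A programme may lower the number of affected teeth per child without changing how many children have any. Study design treats rejection of the null as a strong case for going on to Phase III, so the measure to which the null belongs bears on that decision. A reader who follows the endpoint list would report a proportion, and one who follows Study design would report a mean. The stated power supports only the second.

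**Working it through.** **Inputs from the article.** N = 150, 33% attrition, two-sided 5% (printed as a 95 percent level), power at least 80%, values 2 and 1.6, single arm tested against a fixed value. Evaluable: 150 × 0.67 = 100.5, taken as 100.

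**Input not in the article.** The variance of the count. Poisson is assumed first (variance = mean), then a range of SDs.

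**1. Reproducing the plan's figure as a mean count (one-sample Poisson)**
- Sample size with the null variance: 2 × ((1.960 + 0.842)/0.4)² = 98.1, so 99 evaluable. Enrolled: 99/0.67 = 148, against 150 stated.
- Power at n = 100, null variance: Φ(0.4/√(2/100) − 1.960) = Φ(0.868) = 80.7%.
- Power at n = 100, variance 1.6 under the alternative: Φ((0.4 − 1.960 × √(2/100))/√(1.6/100)) = Φ(0.971) = 83.4%.

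The stated size and power are consistent with a mean count.

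**2. Could 2 and 1.6 be percentages?** At 2% against 1.6%, power with 100 children is about 3%, and about 9,025 evaluable children would be needed for 80%. This reading does not fit.

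**3. Power for a prevalence.** One-sample, n = 100, assumed 20% relative reduction, so p1 = 0.8 × p0. Power = Φ((p0 − p1 − 1.960 × √(p0(1 − p0)/n))/√(p1(1 − p1)/n)).

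| Assumed reference prevalence | Target | Power, normal approximation | Power, exact binomial |
|---|---|---|---|
| 20% | 16% | 15% | 11% |
| 43% | 34.4% | 41% | 35% |
| 60% | 48% | 68% | 62% |
| 70% | 56% | 84% | 82% |
| 80% | 64% | 96% | 94% |

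The 43% is the Background figure from the Northern Territory. It is not the trial's reference rate, which Study design says is informed by New South Wales data.

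**4. Sensitivity of the mean-count power to the SD.** One-sample, n = 100: power = Φ(0.4 × √100/SD − 1.960).
- Largest SD that keeps 80%: 4/(1.960 + 0.842) = 1.43. A Poisson mean of 2 has SD √2 = 1.41, which leaves almost no margin.
- SD 2: Φ(0.040) = 52%, and 197 evaluable are needed for 80%.
- SD 3: Φ(−0.627) = 27%, and 442 evaluable are needed for 80%.

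**The case against.** The strongest reply is that this is one estimand with the wrong label. Study design explains ECC in terms of teeth, calls the target a mean score, and arrives at an N that fits a one-sample test of a mean. Statistical analysis refers to a rate. Read together, the intended measure can be recovered. This stands, and it rules out three stronger readings.

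- A reader might infer that the primary test cannot be run. That is true only if prevalence is taken as a proportion. As a mean count, the test can be run and 150 is consistent with it.
- A reader might infer that the wording lets the result decide the primary endpoint. The only null stated is 2, which fits only the mean, so the planned test has no rival proportion test to switch to. The risk is smaller than it looks.
- A reader might infer that the trial is underpowered for a prevalence, citing 41% at 43%. The article gives no reference prevalence for this population. Over assumed values of 20% to 80% the power runs from 15% to 96%, and it passes 80% near 70%. The supportable statement is that power for a prevalence is unstated.

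A further reply is that an unseen analysis plan may settle the matter. That would answer an omission. Here the article itself prints an endpoint and a null value that are incompatible.

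**Conclusion.** The point holds. The endpoint, the null value and the power statement do not agree as written, and this concerns the primary analysis. The figures belong to a mean count of affected teeth per child. On that scale, about 100 evaluable children give 81% to 83% power, provided that counts are Poisson. The 80% cannot be claimed for a prevalence, because no null, target or power is given on that scale.

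Correcting the label does not by itself secure the 80%. That depends on an SD of about 1.43 or less, which the article neither states nor supports. The results for a prevalence rest on an assumed 20% relative reduction and assumed reference values.

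**What to change.** In Methods/Design (opening text and endpoint list), Study design and Statistical analysis, replace prevalence with the mean number of decayed, missing and filled primary teeth per child at 30 months. Apply the null of 2 and the target of 1.6 to that mean. Make the proportion of children with any affected tooth a named secondary endpoint with its 95% confidence interval.

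State the SD or variance assumption behind the power, preferably from the reference data, and restate the power if the counts are overdispersed.

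If the sponsor prefers the proportion as primary, replace 2 and 1.6 with proportions taken from the reference data and restate the power on that scale.

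Cost: no new data are needed, since both measures come from the same 30-month examination. The change may go beyond wording, because the restated power may be less favourable. At SD 2, for example, 80% power would need 197 evaluable, or 197/0.67 = 294 enrolled, against the potential sample of 216 given under Recruitment.

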**Methods/Design:**

This is a Phase II single arm trial designed to gather information on the effectiveness of a dental health education program for Aboriginal children aged 6 months, followed over 2 years. The program will deliver advice from Aboriginal Health Workers on tooth brushing, diet and the use of fluoride toothpaste to Aboriginal families. Six waves of data collection will be conducted to enable estimates of change in parental knowledge and their views on the acceptability of the program. The Aboriginal Health Workers will also be interviewed to record their views on the acceptability and program feasibility. Clinical data on the child participants will be recorded when they are 30 months old and compared with a reference population of similar children when the study began. Latent variable modeling will be used to interpret the intervention effects on disease outcome.

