**Figure 3 F3:**
[figure not shown]
Potential Structural Equation Model.

Therefore the following will be tested:

i. the (lag 1) effect of fluoride intervention on the subsequent oral health assessment (parameters a_1_, a_2_ a_3_);

ii. a test of stability or equivalence of effect by constraining the parameters a_1_, a_2_ a_3_ (solid lines) to be equal and examining the significance of loss of ‘close fit
[42]’.

iii. a test of the longer term effect (lag 2) of fluoride intervention beyond immediate subsequent oral health assessment controlling for lag 1 effects, as shown by parameters b_1_ and b_2_(dotted line).If these parameters are shown to be significant in this more complex model then an additional enquiry can be performed to test for the equivalence of these two lag 2 coefficients.

Although the health education intervention builds over 2 years the essentials of the appropriate health behaviours are built into the first 3 visits (shaded rectangle in Figure
3), controlling the night time bottle, reducing sugar consumption between meals, using a toothbrush, and applying fluoride toothpaste twice a day. Effectiveness is measured in terms of the caries screening and the final (30 month) full dental examination.

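### The longitudinal model cannot give unbiased estimates of the intervention's effect in a one-arm trial; its paths are associations with reported fluoride use

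*Protocol article*

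**What the plan says.** The Abstract describes the design: "This is a Phase II single arm trial designed to gather information on the effectiveness of a dental health education program". It also gives the modelling a causal role: "Latent variable modeling will be used to interpret the intervention effects on disease outcome".

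The Statistical analysis section lists three advantages of repeated waves. The second is "reliable baseline latent variables of fluoride use and oral health (reducing bias of measurement error"). The third is that the design will "enable the testing of growth models and unbiased parameter estimation of the fluoride intervention using resampling methods (bootstrapping"). The reason given for the third is: "This third improvement would be made possible by controlling for concurrent baseline disease levels".

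The list after Figure 3 commits to testing lag-1 and lag-2 parameters, the first of them described as the "effect of fluoride intervention on the subsequent oral health assessment". The Discussion then presents the model as a means of testing whether the program works.

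The only comparison group described is a set of similar 30-month-old children from the same communities in the program's first year. The article describes no repeated waves for them.

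**The concern.** A model fitted to children who are all offered the program has no contrast between program and no program. If a variable labelled fluoride intervention differs between children, it differs because families took up the advice, or reported doing so, to different degrees. That is self-selected behaviour, and its link with later caries can arise from other things those families do.

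The article promises more than this. It calls the estimate unbiased and gives bootstrapping and control for earlier disease as the reasons. Neither supplies that property. If the text is followed as written, a difference between families who report more fluoride use and families who report less could be published as an effect of the program.

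**Working it through.** **Inputs from the Protocol article**

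- One arm (Abstract).
- Entry at 6 months with two years of follow-up (Study design).
- 150 children with up to 33% attrition (Study design): 150 × (1 − 0.33) = 100.5, so about 100. Recruitment allows up to 216: 216 × 0.67 = 144.7, so about 145.
- Behaviour data come from a questionnaire that the health workers complete with families. It includes bottle and diet items (Data collection).
- The first three visits together deliver bottle control, less sugar between meals, toothbrushing and fluoride toothpaste (text after Figure 3).
- The only adjustment named is for disease level (Statistical analysis).

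The model has no numerical target of its own to reproduce. The primary sample size does reproduce. For a one-sample test of a Poisson mean of 2 against 1.6 with 100 children (the Poisson variance is my assumption), power is Φ[(0.4 − 1.96√(2/100)) / √(1.6/100)] = Φ(0.123/0.126) = 0.83, against the stated minimum of 80%. The present point does not touch that figure.

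**Step 1: what can vary.** Offer of the program equals 1 for every child. In a regression it duplicates the intercept: the two columns have rank 1, so no coefficient for the program itself can be estimated. What can be estimated is a coefficient for uptake or reported use.

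**Step 2: does the named adjustment make that coefficient unbiased?** Take an unmeasured family factor U with variance 1:

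- fluoride use F has variance 1 and correlation l with U
- prior-wave caries Y1 = −gU + error (SD 0.9)
- later caries Y2 = 0.5·Y1 − gU + error (SD 0.9), so the true effect of F is zero

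The large-sample coefficient of F is:

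- adjusting for a baseline that does not vary: −1.5·g·l
- adjusting for prior-wave caries: −g × 0.81·l / [0.81 + g²(1 − l²)]

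For g = 0.3 and l = 0.5, the second is −0.3 × 0.405/0.8775 = −0.138.

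The simulation used 400 trials of 100 children with 200 bootstrap resamples each. Coverage is for the model adjusted for prior-wave caries.

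| g, l (assumed) | Constant baseline: formula / simulated | Prior-wave adjusted: formula / simulated | Coverage of nominal 95% bootstrap interval |
|---|---|---|---|
| 0, 0 | 0 / -0.001 | 0 / -0.001 | 93% |
| 0.2, 0.3 | -0.090 / -0.084 | -0.057 / -0.055 | 89% |
| 0.3, 0.5 | -0.225 / -0.221 | -0.138 / -0.135 | 69% |
| 0.4, 0.6 | -0.360 / -0.369 | -0.213 / -0.219 | 39% |

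**Step 3: reading the table.** F and Y are measured without error here, so correcting for measurement error would not help. Adjusting for prior-wave disease reduces the bias but does not remove it. The bootstrap interval is centred on the biased value. A larger sample (145 rather than 100) would narrow the interval around that same value.

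**Step 4: direction.** The sign comes from my choice of l. Reversing it gives +0.138 in the worked case. This is an ordinary regression with continuous variables, not the trial's model, and the confounding strengths are assumptions.

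**The case against.** Several counter-arguments are sound and limit the point.

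- **Phase III.** A reader might infer that a biased path would drive the decision to proceed or the Phase III effect size. The document does not support that. Study design ties the case for Phase III to rejecting the null hypothesis, and Statistical analysis defines the primary test as the 30-month rate against 2. Neither mentions the structural equation model.
- **Baseline.** A reader might infer that the adjustment is empty, because children enter at 6 months ("The study is designed to monitor a longitudinal oral health education program for Aboriginal children aged 6 months followed for 2 years") and the program centres on "using fluoride toothpaste from 9 months of age". Low fluoride use at entry is plausible, but the article gives no 6-month figure for fluoride use or disease. The phrase about concurrent baseline disease may also mean disease at the start of each lag, which repeated screening supplies. The point therefore must not rest on an uninformative baseline, and the prior-wave column of the table shows that it need not.
- **Direction.** It is tempting to say that the bias favours the program. Advice is tailored to the child's dental needs, so families of children with worse teeth could use more fluoride, and that would push the other way.
- **Figure 3.** The figure is not shown and is offered only as a possible model. Its shaded block may already contain bottle and diet. Prescribing a different starting wave, dropped variables or a particular estimator would go beyond what can be seen. The outcome is also not only a positive/negative screen, since the full 30-month examination is used as well.
- **Context.** The surrounding argument concerns recall, measurement error and two-wave designs, where repeated waves do help.

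None of this rescues the claim itself. The statement about unbiased estimation is not conditional on Figure 3, the list after the figure says that the effects will be tested, and neither stated mechanism removes confounding.

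**Conclusion.** The point holds. The article attributes to the model a property that a one-arm design cannot give it. The lag-1 and lag-2 paths are associations between uptake or reported fluoride use and later caries, open to confounding by the other behaviours taught at the same visits and by family circumstances. This conclusion needs only the single arm and the absence of untreated children with repeated waves. It does not depend on the content of Figure 3, on nil disease or fluoride use at 6 months, or on the simulation.

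The size and direction of the bias cannot be determined from the document. The range of -0.06 to -0.22 shows only that adjusting for earlier disease and bootstrapping can leave material bias under assumed confounding. The harm is confined to the interpretation promised in the Abstract, Statistical analysis and Discussion. The primary analysis and its sample size stand apart from it.

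**What to change.** 1. In Statistical analysis, delete the word *unbiased* and state that bootstrapping is used for interval estimation.
2. In the Abstract, Statistical analysis (including the list after Figure 3) and Discussion, describe the modelled paths as exploratory associations between reported fluoride toothpaste use and later caries, not as effects or efficacy of the program.
3. Include the bottle and diet items already collected as covariates, if the model does not already contain them.
4. State that the structural equation model does not establish program efficacy, and that the efficacy conclusion rests on the primary 30-month comparison.

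This needs no new data and no change to the sample size or primary analysis. The cost is a more modest claim for the model. Adding measured covariates reduces confounding only as far as those items capture it, so the exploratory label is needed either way.
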